### Eligibility criteria and recruitment

Full eligibility criteria for the study are listed in box 2. Patients are eligible if aged 6–17 years with new-onset (<6 months) treatment naïve luminally active and/or perianal fistulising CD diagnosed as per revised Porto criteria^21^ receiving steroids or EEN for induction of remission with wPCDAI >40 or CRP >2 times upper limit of normal at diagnosis. Eligible definitions of disease behaviour were derived from the Paris classification.^22^ Informed consent from must be obtained prior to participation in the study. Patients are excluded in cases of previous use of IBD-related medications, pregnancy or refusal to use contraceptives; disease requiring surgery, contraindications to study medication, exposure to live vaccine within 3 weeks, oral anticoagulant or antimalarial use, current or previous malignancy, significant infection or significant comorbidity.

Box 2Eligibility criteriaInclusion criteriaPatients aged 6–17 years with new-onset (<6 months) treatment naïve active luminal and/or perianal fistulising Crohn’s disease diagnosed using established criteria^21^ requiring steroids or exclusive enteral nutrition (EEN) for induction of remission weighted Paediatric Crohn’s Disease Activity Index (wPCDAI) >40 or C reactive protein (CRP) >2 times upper limit of normal at diagnosis.Luminal active Crohn’s disease (B1) with or without B2 and/or B3 disease behaviour as per Paris classification.^22^Signed informed consent.Exclusion criteriawPCDAI <42.5 at diagnosis, except where CRP >2 times upper normal limit.Lack of induction therapy with steroids or EEN.Previous therapy with any inflammatory bowel disease-related medication other than induction therapy as detailed within this protocol with the exception of 5-aminosalicylic acid preparations.Pregnancy or refusal to use contraceptives during the study period in pubertal patients unless absolute abstinence is confirmed at each study visit.Lactating mothers.Perianal fistulising disease requiring surgical therapy.Patients homozygous for thiopurine methyltransferase (TPMT) mutations or those with TPMT activity <6 nmol/hour/mL erythrocytes or <9 nmol 6-methyl thioguanine (6MTG)/g Hb/hour, unless they qualify as high-risk patients.Evidence of undrained and uncontrolled abscess/phlegmon.Contraindication to any drugs used in the trial (including intolerance/hypersensitivity or allergy to study drugs (thiopurines, methotrexate or adalimumab)).Current or previous malignancy.Serious comorbidities (eg, renal insufficiency, hepatitis, respiratory insufficiency) which may interfere with drug therapy or interpretation of outcome parameters or will make it unlikely that the patient will complete the trial.Infection with mycobacterium tuberculosis, hepatitis B or C, HIV.Moderate to severe heart failure (New York Heart Association class III/IV).Oral anticoagulant therapy, antimalarial therapy.Live vaccine exposure (including yellow fever) less than 3 weeks prior to inclusion.

The planned start date for the study is January 2017 with planned end June 2022.

#### Screening visit (visit 0)

The screening visit allows for assessment of eligibility for inclusion in the study, evaluation of the patient’s response to induction therapy if already commenced, commencement of induction therapy where not commenced, and acquisition of consent and assent.

##### Induction therapy

All enrolled patients receive either corticosteroids or EEN as induction as determined by the clinical team and the patient/caregiver. For EEN any balanced formula (polymeric or elemental) administered orally or via nasogastric tube is permitted and should be prescribed for 6–8 weeks. Tapering of steroids is at the discretion of the prescribing clinician. Adaptation of induction therapy (eg, dose increase of steroids or return to EEN) or crossover from one induction therapy to the other is permitted in order to achieve remission, however, patients must have discontinued their induction therapy by week 12. If induction therapy is not discontinued by week 12, the patient is considered a treatment failure, with the protocol for this detailed below.

#### Inclusion visit and risk group allocation (week 5±3 weeks; visit 1)

In order to incorporate response to initial induction therapy within the risk stratification criteria, inclusion and risk group allocation is performed at week 5±3 weeks of induction therapy. Data from the screening visit are reviewed with ineligible patients excluded and patients are then stratified into the high or low risk group (table 1) based on the European Crohn’s and Colitis Organisation/European Society for Paediatric Gastroenterology, Hepatology and Nutrition consensus guidelines.^1^ Patients with perianal fistulising disease at diagnosis are auto allocated to the high-risk group regardless of other factors at inclusion visit. All other patients are allocated to the low-risk group. Patients with low thiopurine methyltransferase (TPMT) activity or homozygous mutations are excluded should they be categorised as low risk.

### Randomisation and treatment allocation

Randomisation is undertaken following allocation to high or low-risk group at week 5±3 weeks. This process uses an integrated module within the electronic case report form (CRF) system. Within both the high and low-risk groups patients are 1:1 randomised to MTX vs ADA or AZA/6MP, respectively, in blocks of four stratified by EEN or steroid induction therapy. Code for randomisation is prepared and held by the central coordinating site and site coordinators are then informed of the results. Immunomodulator or biological therapy should be commenced within 2 weeks of randomisation as per the protocol outlined in table 2.

**Table 2 T2:** Medication protocol for low and high-risk patients following randomisation

	Therapy	Route	Dose	Notes
Low risk protocol	Methotrexate	SC	15 mg/m^2^ body surface area weekly (max dose 25 mg).	Ondansetron 4–8 mg orally 1-hour preinjection and folic acid 15 mg (5 mg in patients <20 kg) 3 days postinjection are recommended for all patients.
	**Versus**			
	Azathioprine	PO	2.5 mg/kg (rounded down to nearest 12.5 mg).	Half calculated dose for TPMT heterozygotes/activity 6–9 nmol/hour/mL.
	**OR**			
	6-Mercaptopurine	PO	1.5 mg/kg (rounded down to nearest 12.5 mg).	Half calculated dose for TPMT heterozygotes/activity 6–9 nmol/hour/mL.
High-risk protocol	Methotrexate	SC	15 mg/m^2^ body surface area weekly (max dose 25 mg).	Ondansetron 4–8 mg orally 1-hour preinjection and folic acid 15 mg (5 mg in patients <20 kg) 3 days postinjection are recommended for all patients.
	**Versus**			
	Adalimumab (Humira)	SC	160 mg then 80 mg after 2 weeks then 40 mg every 2 weeks thereafter (patients >35 kg). 120 mg then 80 mg after 2 weeks then 40 mg every 2 weeks thereafter (patients 25–35 kg). 80 mg then 40 mg after 2 weeks and 20 mg every 2 weeks thereafter (patients <25 kg).	

PO, Oral; SC, subcutaneous; TPMT, thiopurine methytransferase.

AZA/6MP and MTX are prescribed and dispensed according to local guidelines. ADA (Humira) is provided by AbbVie. Cointerventions are prohibited.

### Follow up visits (visit 2, 3, 4, 5 and 6)

Patients are followed up at prespecified intervals (figure 1) with a window of ±2 weeks. A telephone call is undertaken at week 4 following initiation of induction in order to support patient compliance with induction regime and advise weaning where appropriate. Data as described in box 3 are collected at each consultation. Patients’ compliance with therapy is determined at each face-to-face follow-up visit by pill and vial counts plus by patients’ reporting.

Box 3Standard requirements for each study visitAn explicit history of illness since last visit, including review of symptoms, medications (including compliance check) and adverse events.Physical examination weighted Paediatric Crohn’s Disease Activity Index (wPCDAI), physician global assessment and PCDAI scoring.Anthropometrics (height measured using a calibrated wall mounted stadiometer).Blood tests.White blood cells.Absolute neutrophil count.Haemoglobin.Haematocrit.Platelet count.Erythrocyte sedimentation rate.C reactive protein.Amylase.Albumin.Aspartate transaminase.Alanine transaminase.Conjugated bilirubin.Gamma glutamyl transferase.Stool samples for faecal calprotectin and microbiome analysis.Health economic parameters (EQ-5D-Y proxy 1; EQ-5D-Y; EQ-5D-5L; WPAI:Crohn’s disease; school attendance questionnaire).Quality of life evaluation (IMPACT 3).Urine human chorionic gonadotropin in all female patients of childbearing potential.Confirmation of contraception use or of absolute abstinence in all patients.

Remission is defined as wPCDAI≤12.5, normal CRP (≤1.5 times upper normal range) and being free of steroids or EEN. Once remission is achieved and induction therapy is discontinued, a patient is considered to be failing treatment or experiencing a relapse in the following circumstances:

wPCDAI >40.CRP >2 times upper normal limit in the absence of any clear infectious process.wPCDAI >12.5 but <40 and/or CRP >1.5 times but <2 times over upper normal limit at two consecutive visits within 2–8 weeks.Development of CD-related complications, for example, fistulisation.Requirement for additional CD-specific medication/surgery since last study visit.

A patient will also be considered a treatment failure should induction therapy be continued at week 12. In addition, the treating clinician may escalate treatment at any time point independent of wPCDAI score if it is felt that the patient is experiencing a relapse.

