### Study end points

Patients are followed up for 12 months postrandomisation. The primary end point of the study is sustained steroid or EEN-free remission at 12 months, defined as weighted Paediatric Crohn’s Disease Activity Index (wPCDAI) ≤12.5 and C reactive protein (CRP) ≤1.5 fold upper limit without a relapse or need for EEN/steroids since week 12.

Secondary end points include comparison of time to first relapse, remission at 12 weeks, growth, adverse events, health-related quality of life and patient-reported outcomes between the two treatment arms within each risk group but also between low and high risk MTX treated patients (a full list of secondary endpoints can be found in box 1). The TUMMY CD (patient-related outcome measure) was originally included as a secondary end point but has been withdrawn as the original timetable of development and validation of the score has not been met so it was not ready in time to be included. The study also aimed to evaluate clinical predictors for response, including genomic and serological markers and results of drug monitoring (MTX and ADA concentrations) metabolites (6-thioguanine (6-TG) and 6-methylmercaptopurine (6-MMP) in AZA/6MP) and antidrug antibodies (ADA) in relation to adherence, toxicity and response. The ancillary study additionally aimed to evaluate the efficacy of ADA in patients treated from inclusion (top-down) versus patients switched to ADA due to immunomodulator failure (step-up). Further outcome measures are detailed in box 1.

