#### Dose optimisation and therapeutic drug monitoring

Drug monitoring is undertaken as detailed below. In addition to this, samples for drug monitoring should be collected at the time of medication cessation in the event of drug discontinuance due to adverse effect or loss of response. Potential adaptations to therapies which may be made at specific follow-up visits are detailed in box 4.

Box 4Potential adaptations to therapies at follow-up visitsMonth 2 (visit 2)Failure to discontinue induction therapy by week 12Offer switch to the ancillary study (adalimumab (ADA) step-up) to those prescribed methotrexate (MTX) or azathioprine (AZA)/6-mercaptopurine (6MP), or an increase in dose frequency to weekly in those prescribed ADA.Alternatively, the patient may leave the study and receive therapies as per the discretion of the treating clinician.Months 4, 6, 9 and 12 (visits 3, 4, 5 and 6)Thiopurine non-response.Protocol as per metabolite levels (detailed in table 3).Thiopurine intolerance (except pancreatitis).Switch to alternate thiopurine (AZA to 6MP or vice versa) or split dose to provide twice daily (BD) dosing.Thiopurine failure (any exacerbation despite dose optimisation/pancreatitis/cytopaenia).Offer switch to ancillary study (ADA STEP-up) or exit study.MTX intolerance or failure (any exacerbation or elevation of liver enzymes as detailed below).Offer switch to ancillary study (ADA STEP-up) or exit study.ADA failure (any exacerbation).Increase frequency to weekly dosing.

**Table 3 T3:** Azathioprine dose adjustments based on metabolite levels

Result	Action
6-TG <150	Consider non-compliance; repeat sample at subsequent visit and increase dose if low 6-TG confirmed (+25 mg or +12.5 mg if dose <50 mg).
6-TG 150–800	No adaptation.
6-TG >800	Decrease dose if repeat sample at subsequent visit confirms high 6-TG (−25 mg or −12.5 mg if dose <50 mg).
6-MMP >8000 or signs of hepatotoxicity	Stop medication—switch to ancillary study. Erythrocyte lysate sample frozen at −80°C and shipped to central lab at end of study for thiopurine nucleotides.

6-MMP, 6-methylmercaptopurine.

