#### Unscheduled visits

Unscheduled visits may be arranged based on clinical requirements. As for scheduled visits per protocol treatment adaptions are possible if intolerance or failure of the study drug is detected. Subsequent scheduled visits will not be changed after an unscheduled visit.

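### Confirming an intermediate relapse does not fit the visit schedule, and the relapse list presumes prior remission, so disease active until month 9 can count as sustained remission

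*Protocol article*

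**What the plan says.** All references are to the protocol article.

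- **Primary endpoint** (Study end points; Box 1): wPCDAI ≤12.5 and CRP ≤1.5 times the upper limit at month 12, "without a relapse or need for EEN/steroids since week 12". Remission at week 12 is listed in Box 1 as a separate secondary endpoint.
- **Relapse definition** (Follow up visits): the list opens with "Once remission is achieved and induction therapy is discontinued, a patient is considered to be failing treatment or experiencing a relapse". Four of its five criteria act at a single visit: the two thresholds "wPCDAI >40.CRP >2 times upper normal limit in the absence of any clear infectious process", a complication of the disease ("Development of CD-related complications, for example, fistulisation"), and added Crohn's medication or surgery. The fifth, intermediate activity (wPCDAI between 12.5 and 40 and/or CRP between 1.5 and 2 times the upper limit, bounds excluded), needs confirmation: it must be present "at two consecutive visits within 2–8 weeks".
- **Other failure routes** (same section): induction still running at week 12 is treatment failure in its own right, and the clinician may escalate treatment at any time.
- **Schedule**: Box 4 gives "Months 4, 6, 9 and 12 (visits 3, 4, 5 and 6"; Box 1 places visits 1 and 2 at months 0 and 2. Each visit has a window of ±2 weeks.
- **Extra visits** (Unscheduled visits): "Unscheduled visits may be arranged based on clinical requirements". Nothing in the article requires one to confirm an intermediate result.

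**The concern.** The word sustained in the primary endpoint is carried almost wholly by the relapse definition. If that definition cannot register intermediate activity at the visits the trial schedules, or does not yet apply to the patient, then a child with active disease for most of the year can be scored the same as one in remission throughout.

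Two things are at stake in both randomised comparisons. Misclassifying failures as successes dilutes the difference between arms. Ascertainment may also differ by arm: whether an intermediate result is confirmed within 2–8 weeks depends largely on a clinician who knows the treatment and decides whether to recall the child. Under Box 4, failure on MTX or thiopurine leads to an offer of the ADA step-up study, while failure on ADA leads to more frequent dosing, so the reasons to look for failure are not the same in each arm. Blinded scoring where possible does not govern who is recalled. The same definition also feeds time to first relapse and the relapse-free remission endpoints in Box 1.

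**Working it through.** **1. The plan's own figure.** Sample size with a two-sided 5% level, 80% power, pooled variance and no continuity correction, divided by 0.90 for loss:
- Low risk, 48% v 70%: 78 per arm; 78/0.90 = 86.7, so 87 (stated 88).
- High risk, 40% v 65%: 62 per arm; 62/0.90 = 68.9, so 69 (stated 68).

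The sample size reproduces to within one patient per arm and is not in dispute.

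**2. Visit gaps against the 2–8 week requirement.** Box 1 measures height at 52 weeks in a 12-month follow-up, so one month is 52/12 = 4.33 weeks. Shortest and longest gaps put the two visits at opposite ends of their windows (∓4 and ±4 weeks).

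| Pair (months) | Nominal | Shortest | Longest | Can it confirm? |
|---|---|---|---|---|
| 2–4, 4–6 | 2 × 4.33 = 8.7 | 4.7 | 12.7 | Only if windows shorten the gap |
| 6–9, 9–12 | 3 × 4.33 = 13.0 | 9.0 | 17.0 | Never |

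With 4-week months instead, the early pairs are 8.0 weeks apart (4–12) and the late pairs 12.0 (8–16). A late pair then qualifies only with both windows fully used. Whether the 2–4 pair lies wholly inside the relapse period depends on where week 12 is counted from; the 4–6 and 6–9 pairs lie inside it on any reading.

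**3. Two hypothetical patients**, both with normal CRP, no complication, no added treatment and wPCDAI ≤12.5 at month 12.
- *Patient A*: in remission at month 4, wPCDAI 30 at months 6 and 9. No single-visit criterion is met. The two-visit criterion fails on the interval unless an extra visit was arranged. Scored as sustained remission.
- *Patient B*: off induction by week 12, wPCDAI 30 at months 2, 4, 6 and 9. Remission has not been reached, so the list does not apply at any of these visits, whatever the gaps. Induction was stopped in time and no steroids or EEN were needed. Scored as sustained remission.

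**4. Values in no band.** A wPCDAI of exactly 40 is neither above 40 nor below 40, and a CRP of exactly twice the limit has the same problem. Box 2 includes wPCDAI above 40 and excludes below 42.5, which implies that 40 is an attainable score next to 42.5.

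**5. Illustration of dilution (assumed).** Suppose a fraction m of true non-responders in each arm is scored as sustained remission, so each rate p becomes p + m(1 − p). The article gives no m. Analysable patients per arm are 88 × 0.9 = 79.2 and 68 × 0.9 = 61.2. At m = 10%:
- Low risk: 0.48 + 0.10 × 0.52 = 0.532; 0.70 + 0.10 × 0.30 = 0.730; difference 0.198.
- High risk: 0.40 + 0.10 × 0.60 = 0.460; 0.65 + 0.10 × 0.35 = 0.685; difference 0.225.

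| m | Power, low risk | Power, high risk |
|---|---|---|
| 0 | 81% | 80% |
| 5% | 77.5% | 76% |
| 10% | 74% | 72% |
| 20% | 66% | 63% |

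**The case against.** A reader might infer that the relapse rule as a whole stops working after month 6. The article does not support that. Four of the five criteria act at any single visit, month 9 included, for a child who has been in remission.

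Nor is half of follow-up lost. The 9–12 pair is moot for the primary endpoint, because intermediate activity at month 12 already fails the month-12 limits. The scheduled pair that both matters and can never confirm is 6–9. For two-monthly visits, a 2–8 week interval may well have been meant to include them, and the nominal excess is only 0.7 weeks.

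The confirmation window together with unscheduled visits can fairly be read as a recall rule, and the clinician may escalate at any time. Patients who never remit are still caught if induction continues at week 12, if steroids or EEN are needed later, or if disease is active at month 12. It would also go too far to say that many high-risk patients start follow-up as Patient B does: Table 1 lists persistent activity as one of several alternative criteria and gives no proportions, and induction may be adapted until week 12. Finally, detailed derivations commonly sit in an analysis plan, which is not shown.

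All of this narrows the point. What stands is that recall is permitted but not required, that Patients A and B satisfy the endpoint as written, and that an analysis plan following these stated rules would inherit the conflict.

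**Conclusion.** The point holds in a limited form. The intermediate criterion cannot be met by the scheduled month 6 and 9 visits (at least 9.0 weeks apart on calendar months), and at nominal timing the 2–4 and 4–6 pairs miss it too. Separately, the condition of prior remission, with no requirement for remission at week 12, lets a first remission at month 12 count as sustained.

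Misclassification needs intermediate activity without added treatment, steroids or EEN, no confirming extra visit where the child had previously remitted, and both limits met at month 12. How often that happens, and whether it differs by arm, cannot be derived from the article. The power figures show only what an assumed equal fraction would cost, and no arm-specific bias can be sized or given a direction. The unassigned values of 40 and twice the limit are a drafting gap of small effect.

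**What to change.** Reconcile Study end points, Box 1, Follow up visits, Box 4 and Unscheduled visits for endpoint derivation only, leaving clinical management untouched:

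1. Count as not sustained any patient above the trial's own remission limits (wPCDAI >12.5 or CRP >1.5 times the upper limit) at two consecutive scheduled visits after week 12, whatever the interval and whether or not remission was reached before. Keep the existing infection exemption for CRP.
2. Apply the single-visit criteria for the endpoint regardless of prior remission.
3. Assign wPCDAI of exactly 40 and CRP of exactly twice the limit to a band.
4. Rest the main analysis of the two-visit criterion on scheduled visits, so that discretionary visits do not give one arm more chances to fail, and report a sensitivity analysis that also uses unscheduled visits.

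The change should be made before outcome data are reviewed. wPCDAI and CRP are already collected at every visit (Box 3), so the cost is wording and programming. The downside is that remission rates may come out somewhat lower in both arms.

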#### Dose optimisation and therapeutic drug monitoring

Drug monitoring is undertaken as detailed below. In addition to this, samples for drug monitoring should be collected at the time of medication cessation in the event of drug discontinuance due to adverse effect or loss of response. Potential adaptations to therapies which may be made at specific follow-up visits are detailed in box 4.

Box 4Potential adaptations to therapies at follow-up visitsMonth 2 (visit 2)Failure to discontinue induction therapy by week 12Offer switch to the ancillary study (adalimumab (ADA) step-up) to those prescribed methotrexate (MTX) or azathioprine (AZA)/6-mercaptopurine (6MP), or an increase in dose frequency to weekly in those prescribed ADA.Alternatively, the patient may leave the study and receive therapies as per the discretion of the treating clinician.Months 4, 6, 9 and 12 (visits 3, 4, 5 and 6)Thiopurine non-response.Protocol as per metabolite levels (detailed in table 3).Thiopurine intolerance (except pancreatitis).Switch to alternate thiopurine (AZA to 6MP or vice versa) or split dose to provide twice daily (BD) dosing.Thiopurine failure (any exacerbation despite dose optimisation/pancreatitis/cytopaenia).Offer switch to ancillary study (ADA STEP-up) or exit study.MTX intolerance or failure (any exacerbation or elevation of liver enzymes as detailed below).Offer switch to ancillary study (ADA STEP-up) or exit study.ADA failure (any exacerbation).Increase frequency to weekly dosing.

**Table 3 T3:** Azathioprine dose adjustments based on metabolite levels

Result	Action
6-TG <150	Consider non-compliance; repeat sample at subsequent visit and increase dose if low 6-TG confirmed (+25 mg or +12.5 mg if dose <50 mg).
6-TG 150–800	No adaptation.
6-TG >800	Decrease dose if repeat sample at subsequent visit confirms high 6-TG (−25 mg or −12.5 mg if dose <50 mg).
6-MMP >8000 or signs of hepatotoxicity	Stop medication—switch to ancillary study. Erythrocyte lysate sample frozen at −80°C and shipped to central lab at end of study for thiopurine nucleotides.

6-MMP, 6-methylmercaptopurine.

